# Online parent-targeted cognitive-behavioural therapy intervention to improve quality of life in families of young cancer survivors: study protocol for a randomised controlled trial

**DOI:** 10.1186/s13063-015-0681-6

**Published:** 2015-04-11

**Keywords:** Parent, carer, cancer, survivorship, intervention study, randomised controlled trial, psychological adaptation, quality of life, cognitive-behavioural therapy, Internet, E-health

## Abstract

**Background:**

Due to advances in multimodal therapies, most children survive cancer. In addition to the stresses of diagnosis and treatment, many families are now navigating the challenges of survivorship. Without sufficient support, the ongoing distress that parents experience after their child’s cancer treatment can negatively impact the quality of life and psychological wellbeing of all family members.

**Methods/Design:**

The ‘Cascade’ (*C*ope, *A*dapt, *S*urvive: Life after *C**A*nc*E*r) study is a three-arm randomised controlled trial to evaluate the feasibility and efficacy of a new intervention to improve the quality of life of parents of young cancer survivors. Cascade will be compared to a peer-support group control and a 6-month waitlist control. Parents (n = 120) whose child (under 16 years of age) has completed cancer treatment in the past 1 to 12 months will be recruited from hospitals across Australia. Those randomised to receive Cascade will participate in four, weekly, 90-minute online group sessions led live by a psychologist. Cascade involves peer discussion on cognitive-behavioural coping skills, including behavioural activation, thought challenging, mindfulness and acceptance, communication and assertiveness skills training, problem-solving and goal-setting. Participants randomised to peer support will receive four, weekly, 90-minute, live, sessions of non-directive peer support. Participants will complete measures at baseline, directly post-intervention, one month post-intervention, and 6 months post-intervention. The primary outcome will be parents’ quality of life. Secondary outcomes include parent depression, anxiety, parenting self-agency, and the quality of life of children in the family. The child cancer survivor and all siblings aged 7 to 15 years will be invited to complete self-report quality of life measures covering physical, emotional, social and school-related domains.

**Discussion:**

This article reviews the empirical rationale for group-based, online cognitive-behavioural therapy in parents of children who have recently finished cancer treatment. The potential challenges of delivering skills-based programs online are highlighted. Cascade’s videoconferencing technology has the potential to address the geographic and psychological isolation of families after cancer treatment. Teaching parents coping skills as they resume their normal lives after their child’s cancer may see long-term benefits for the quality of life of the family as a whole.

**Trial registration:**

ACTRN12613000270718 (registered 6 March 2013).

**Electronic supplementary material:**

The online version of this article (doi:10.1186/s13063-015-0681-6) contains supplementary material, which is available to authorized users.

## Background

Although rare, cancer is a leading cause of death in children in developed countries [1]. After the shock of diagnosis, parents face the difficult dual challenges of supporting their child through debilitating treatment, whilst grappling with the possible death of their child [2]. Due to improved multimodal therapies, most children survive cancer [3]. It is often only when treatment ends that parents process the experience, at the very time when hospital-based psychosocial support is diminished [4]. Despite the acknowledged positive aspects of treatment completion [5,6], this is a vulnerable time for some parents, who can experience worsening quality of life (QoL), anxiety, depression, and feelings of helplessness [7,8]. Parents living in rural/remote areas appear most at risk of these poor outcomes [9]. Major themes of difficulty in the post-treatment period can include fear of cancer recurrence, isolation, and loneliness, with substantial unmet needs for information about relapse surveillance and how to ‘return to normality’ [10-12].

In the face of cancer, parents may lack the coping skills needed to manage the demands of their child’s treatment and survivorship, and others can develop maladaptive coping strategies under pressure [13]. Parental psychological adjustment problems may jeopardise their capacity to provide the ‘secure base’ that children need in times of stress [14] and can lead to less effective parenting [15,16]. Even after their child has been cured, distressed parents may express more anger toward their surviving child [17], listen less to their children [18], and have more negative parent–child interactions [19]. These parenting approaches may result in more behaviour problems [15] and distress [20,21] in young cancer survivors and their siblings [22]. The impact of poor parent coping may extend for years, with evidence that even 10 to 15 years post-diagnosis, coping in child cancer survivors may still be related to their mother’s coping [23]. Best-practice mental health interventions for children with cancer therefore need to target the family, not just the patient [24].

Evidence-based psychological interventions have the potential to reduce parental mental health burden in the ‘coming off treatment’ phase, thus curtailing longer-term difficulties. Best-practice interventions target modifiable processes associated with parents’ poor adaptation to their child’s cancer. For example, parents of children with cancer can use more ruminative thinking and defensive coping strategies [13], both of which can create conflict and poor family cohesion [25]. Interventions that increase parents’ use of adaptive coping strategies in the face of their child’s cancer may reduce their risk of depression and anxiety [26] and enhance their parenting skills [17]. Improving parents’ communication skills can also promote adaptive functioning in children with cancer [27]. Parents’ capacity to proactively solve problems and seek help when needed is also modifiable, yielding improved outcomes for children with cancer when targeted [13,28].

Skills-based interventions can be effective in parents of children with cancer, yielding medium-large effects [29]. However, few interventions have been rigorously evaluated. Most are also implemented face-to-face, limiting benefits to rural and remote families. It is clear that online cognitive-behavioural therapy (CBT) programs can be effective, with meta-analyses reporting medium-large effects for anxiety [30] and depression [31]. Trans-diagnostic programs that target co-morbid anxiety and depression may also be effective when delivered online [32]. Online programs also have the potential to reduce distress and improve wellbeing in those who care for someone with a medical condition [33]. Furthermore, group-based support is cost-effective and provides a unique context in which individuals can provide each other with emotional support, reflect on the commonalities of their experiences, and share resources [34]. Given that no efficacious, online programs currently exist to provide support for Australian parents at this recognised critical adjustment period [35], we developed a tailored intervention, ‘Cascade’, to meet their needs.

## Methods/Design

The Cascade study is a multi-site, randomised controlled trial (RCT) to assess the feasibility and efficacy of a new, online, CBT-based intervention for the parents or legal guardians (hereafter referred to as ‘parents’) of young cancer survivors (see Additional file 1 for a list of participating centres and ethical bodies). Parents of children under 16 years of age who have completed cancer treatment with curative intent and achieved remission in the past 12 months will be recruited and randomised to one of three arms: i) Cascade, ii) a peer-support group (PSG) control, or iii) a 6-month waitlist control. Informed consent will be obtained from all participants. The 1- to 12-month timeframe was chosen to maximise the benefit to participants, by delivering the coping skills intervention early in their child’s survivorship period. The intervention, named ‘CASCAdE’ (*C*ope, *A*dapt, *S*urvive: Life after *CA*nc*E*r), is delivered live, in real-time, to groups of 3 to 5 parents by a psychologist (hereafter referred to as ‘facilitator’) in four, weekly online sessions. Participants also receive an online introductory session with the facilitator before the group commences and a ‘booster’ session one month after the end of the group to facilitate consolidation of skills.

Cascade will be compared with the active PSG control in order to assess the relative benefits of peer-based support and contact with any additional psychological benefits gained from learning structured, skills-based coping strategies. ‘Peer-support’ type models of support are ubiquitous in community settings, yet few PSGs have been rigorously evaluated [36]. Consequently, little evidence exists to support the appropriateness of PSGs alone in addressing distress in parents of children with cancer. The PSG arm holds constant the amount of treatment contact, human interaction variables (such as facilitator warmth and interaction between participants), as well as controlling for participants’ expectations of receiving some form of treatment [37].

This study employs a three (treatment condition) by four (assessment point) factorial design. All participants will complete an assessment battery at baseline (T1: recruitment), immediately after participation in Cascade or the PSG control (T2), 5-weeks post-intervention/1-week post-booster session (T3), and 6-months post-intervention (T4). The waitlist group will be assessed at the same time points. After the 6-month waitlist period, waitlisted parents will be re-randomised to either Cascade or the PSG. They will complete a final, additional, assessment battery immediately after their group program (T5). All the children ages 7 to 15 years of participating parents (including the child cancer survivor and any siblings) will be invited to complete measures of depression, anxiety and peer relationships at the same time points as their parents (see Table 1).

**Table 1 Tab1:** **Assessment schedule for the cascade study**

**Measure**	**Intake**	**Q1** ^**a**^	**During intervention** ^**b**^	**Q2** ^**c**^	**Q3** ^**d**^	**Q4** ^**e**^	**Q5** ^**f**^
Psychosocial Adjustment to Illness Scale-Interview form (PAIS)	**X**	**-**	**-**	**-**	**-**	**-**	**-**
Demographic data	**-**	**X**	**-**	**-**	**-**	**-**	**-**
Treatment Intensity Scale	**-**	**X**	**-**	**-**	**-**	**-**	**-**
Medical and general functioning^g^	**-**	**X**	**-**	**X**	**X**	**X**	**X**
Paediatric Quality of Life Inventory (PedsQL) Generic Core Scale^h^	**-**	**X**	**-**	**X**	**X**	**X**	**X**
Paediatric Quality of Life Inventory (Family Impact Module)	**-**	**X**	**-**	**X**	**X**	**X**	**X**
EQ-5D-5 L	**-**	**X**	**-**	**X**	**X**	**X**	**X**
Parenting Self Agency Measure (Revised)	**-**	**X**	**-**	**X**	**X**	**X**	**X**
CBT skills use	**-**	**X**	**-**	**X**	**X**	**X**	**X**
PROMIS parent mental health and functioning short-form items^i^	**-**	**X**	**-**	**X**	**X**	**X**	**X**
California Psychotherapy Alliance Scale - Group (CALPAS-G)	**-**	**-**	**-**	**X**	**-**	**-**	**X**
Intervention satisfaction items	**-**	**-**	**-**	**X**	**-**	**-**	**X**
Emotion Thermometers Tool	**X**	**-**	**X**	**-**	**-**	**-**	**-**
Homework Compliance Scale	**-**	**-**	**X**	**-**	**-**	**-**	**-**
Working Alliance Inventory - Short	**-**	**-**	**X**	**-**	**-**	**-**	**-**

^**a**^Q1 = Baseline; ^**b**^During intervention = weekly prior to intervention sessions 2 to 4; ^**c**^Q2 = post-intervention.

^**d**^Q3 = Week 5 follow-up, ^e^Q4 = 6 month follow-up; ^f^Q5 = after waitlist participants have completed the intervention.

^g^Including other psychological support received; ^h^Parent proxy and child self-report; ^i^Items assess parent depression and anxiety symptoms.

### Aims and hypotheses

This RCT aims to assess the following:The feasibility of implementing Cascade nationwide, including the recruitment procedure, response/attrition rates and cost.The efficacy of Cascade in improving the QoL of parents (the primary outcome). Secondary outcomes include parent depression, anxiety, and parenting self-agency, as well as social and emotional functioning of the children in the family.

We hypothesise that delivering Cascade will be feasible and acceptable. We also hypothesise the following:Both the PSG and Cascade participants will show greater improvements in QoL compared with the waitlist control, measured from T1 to T2.Participants who complete Cascade will show greater improvements in their QoL compared to participants who complete the PSG, measured from T1 to T2.

### Participants

This study will recruit 120 parents (approximately 40 in each arm). This sample size will allow medium-to-large differences in parent QoL to be detected with a power of 80% at a two-tailed significance level of 0.05 (assuming Cohen’s d = 0.65 as the difference in change from time 1 to time 2 for any pair of groups, standardised on the pooled within-group standard deviation). This effect size is clinically significant [38]. It is anticipated that approximately 375 parents will need to be approached to achieve a final sample of 120 participants (assuming a 40% response rate and 20% attrition rate).

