#### Statistical analyses

This trial will employ ‘intention-to-treat’ and ‘as-treated’ analyses. Analyses will be based on mixed random-intercept models that will assess differences between the groups in terms of change in QoL from T1 to T2 (the primary analysis), from T1 to T3, and from T1 to T4. Random intercept models, which utilise maximum-likelihood estimation, provide more efficient estimates of effects with unbalanced data than the traditional repeated measures approach [67]. Multiple regression analyses will be conducted using T1 data to identify demographic and other factors that contribute to treatment outcome. Multiple comparisons will be used to test a priori hypotheses and to conduct post-hoc testing, with the alpha rate adjusted using the Holm-Bonferroni method [68].

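### The 80% power is calculated at an unadjusted 0.05, but the three planned contrasts are tested with Holm-Bonferroni; with no true difference above d = 0.65, power is about 68–72%

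*Protocol article*

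**What the plan says.** All references are to the protocol article.

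- **Participants.** The size is given as "This study will recruit 120 parents (approximately 40 in each arm"). The paragraph claims that a medium-to-large effect on parents' quality of life can be "detected with a power of 80% at a two-tailed significance level of 0.05". The effect behind that claim is set out in brackets: "assuming Cohen’s d = 0.65 as the difference in change from time 1 to time 2 for any pair of groups". The scale of d is described there too, as "standardised on the pooled within-group standard deviation". No multiplicity adjustment is mentioned. On the numbers to be invited, the same paragraph reads: "approximately 375 parents will need to be approached to achieve a final sample of 120 participants (assuming a 40% response rate and 20% attrition rate").
- **Aims and hypotheses.** The first efficacy hypothesis is that "Both the PSG and Cascade participants will show greater improvements in QoL compared with the waitlist control", which is two contrasts. The second is that Cascade improves quality of life more than the peer-support group (PSG), which is a third. All three concern change from T1 to T2.
- **Statistical analyses.** The T1-to-T2 comparison is named as the primary analysis. A priori hypotheses and post-hoc tests are both to be handled by multiple comparisons, "with the alpha rate adjusted using the Holm-Bonferroni method".

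**The concern.** The significance level behind the sample size is not the level at which the planned tests are carried out. The three contrasts in the hypotheses are the pairs that the power statement covers, and they are expressly subject to Holm-Bonferroni. Under Holm the smallest of three p-values must fall below 0.05/3 = 0.0167. If it does, the next must fall below 0.025, and only the last is tested at 0.05. A power figure for 0.05 therefore overstates what the design delivers for a given pair, unless the other contrasts are large enough to be rejected first.

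What is at stake is interpretation. The Discussion treats Cascade against peer support alone as a central question with clinical and economic consequences. A non-significant result there would be read as coming from a test with a 20% risk of missing d = 0.65, when the risk may be nearer 30%. Type I error, estimates and confidence intervals are not affected.

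**Working it through.** **Inputs.** From Participants: n = 40 per arm, d = 0.65, two-sided 0.05, stated power 80%. From Aims and hypotheses: three pairwise contrasts. From Statistical analyses: Holm-Bonferroni. Assumption: d is standardised on the SD of the T1–T2 change, so SD = 1 on the d scale.

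**1. The plan's own figure.** The noncentrality is d·√(n/2) = 0.65 × √20 = 2.907. With 78 degrees of freedom the two-sided 0.05 critical value is 1.991, and the noncentral t distribution gives power of 81.9% (82.8% by the normal approximation). The smallest n reaching 80% is 39 per arm by the t calculation and 38 by the normal approximation. So 40 per arm reproduces the stated 80% at an unadjusted 0.05.

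**2. The same sample at the Holm thresholds** (noncentral t):

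| Threshold | Power at d = 0.65 | d detectable with 80% power |
|---|---|---|
| 0.05 | 81.9% | 0.63 |
| 0.025 | 73.2% | 0.70 |
| 0.0167 (first step) | 67.7% | 0.74 |

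Reaching 80% at 0.0167 would take 52 per arm (50 by the normal approximation).

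**3. Full Holm procedure.** The first-step figure is single-step Bonferroni and so a floor. Holm relaxes after each rejection, so power for one pair depends on the other two. The three contrasts were simulated with 40 per arm, SD 1 and t-tests with separate or pooled variance (200,000 replicates). Means are in the order waitlist / PSG / Cascade.

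| True means | Contrast with d = 0.65 | Power under Holm |
|---|---|---|
| 0 / 0 / 0.65 | Cascade–PSG, Cascade–waitlist | 71–72% each |
| 0 / 0.65 / 0.65 | PSG–waitlist, Cascade–waitlist | 71–72% each |
| 0 / 0.325 / 0.65 | Cascade–waitlist | 69% |
| 0 / 0.30 / 0.95 | Cascade–PSG | 75–76% |
| 0 / 0.65 / 1.30 | Cascade–PSG, PSG–waitlist | 81% each |

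The first three rows have no difference above 0.65. The last two follow the order that the hypotheses state, with Cascade best and waitlist worst.

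**4. Attrition.** 375 × 0.40 = 150 parents enter and 150 × 0.80 = 120 remain. Participant recruitment agrees, with five blocks of about 30 opt-ins (5 × 30 = 150). So 120 is the retained number, and 40 per arm is the right n for steps 1 to 3.

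**5. Three-arm closed test as an alternative.** A global 2-df test at 0.05 comes first. If it rejects, each pair is tested at 0.05. Per-pair power at d = 0.65 is 78% with two pairs at 0.65 and one null, and 72% for Cascade–waitlist with PSG midway. Simulated familywise error is about 0.05 under the global and the partial null.

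**The case against.** **Holm is milder than Bonferroni, and the trial's own hypotheses help it.** This stands and limits the point. If Cascade beats PSG by 0.65 and PSG also beats waitlist, Cascade versus waitlist must exceed 0.65. It is then usually rejected first, and Cascade versus PSG keeps about 76–81%. A reader might infer that the planned test has 68–72% power whatever the truth. The document does not support that, because the range requires that no difference exceeds 0.65. Even so, the power statement promises 80% for any pair without assuming a larger effect elsewhere. In the plain case where Cascade works and PSG equals waitlist, Cascade versus PSG has about 72%.

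**At least one rejection remains likely.** With two contrasts at 0.65 that probability is about 82–83%. But the claim is made per pair, so this does not rescue it.

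**The SD scale is not fully specified.** This stands as a caveat. The text describes d as a difference in change and names a pooled within-group SD, without saying whether it is the SD of change or of raw scores. On the raw-score reading, power at 0.0167 would be 51%, 68% or 79% for T1–T2 correlations of 0.3, 0.5 or 0.6. The document gives no correlation.

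**Two stronger readings should not be drawn.** A reader might take the sentence about recruiting 120 literally, remove 20%, and compute power for 32 per arm. The approach figures and the recruitment blocks show that 120 is what remains after loss, so the verb is at most loose. A reader might also put the T3, T4 and post-hoc tests into one large Holm family and arrive at much lower power. The article defines no such family and names T1 to T2 as primary. How families are divided may properly be left to the analysis plan.

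**Conclusion.** The point holds in conditional form. The arithmetic behind the stated 80% is sound, but it belongs to an unadjusted test that the article does not plan to use for its a priori hypotheses. With 40 per arm analysed at T2 and Holm over the three contrasts, power for a true d of 0.65 is:

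- about 68–72% when no pairwise difference exceeds 0.65, where 68% is the first-step floor and 69–72% the full procedure;
- about 76–81% for Cascade versus PSG when Cascade versus waitlist is 0.95 to 1.3.

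The shortfall from the 82% available without adjustment therefore runs from about 14 points (82 − 68) to about 1 point (82 − 81). These figures rest on three assumptions: d is standardised on the SD of change, the Holm family is the three T1–T2 contrasts, and 120 parents contribute T2 data. Attrition is not the cause of the gap.

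**What to change.** **Main change.** Rewrite the power sentence under Participants for the Holm-adjusted test, with 40 per arm analysed at T2. Either of two statements would do:

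- for d = 0.65, power of about 68–72% when no pairwise difference exceeds 0.65, rising to about 76–81% for Cascade versus PSG if Cascade versus waitlist is 0.95 to 1.3; or
- 80% power for d of about 0.74 at the first Holm step.

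Say that d is standardised on the SD of change, if that is what was meant. This is wording only and needs no extra participants. The price is a less favourable stated power.

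**Optional.** For the three primary contrasts, replace Holm with the closed test for three arms (global 2-df test at 0.05, then each pair at 0.05). With exactly three arms it controls the familywise error. It recovers part of the loss (78% against 71–72% with two pairs at 0.65 and one null; 72% against 69% with PSG midway) but does not restore 80% in those cases. It is an analysis amendment in a trial that the Trial status section describes as already recruiting, and its pairwise confidence intervals are not simultaneous. Holm is valid, so this is a choice and not a correction.

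**Minor.** In the same edit, describe 120 as the number retained and not the number recruited, in line with the article's own approach figures.

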#### Inclusion criteria

Eligible parents will meet the following inclusion criteria: i) have a child under 16 years of age who has completed cancer treatment with curative intent in the past 12 months; ii) be able to give informed consent; iii) be able to read English; iv) be able to provide the contact details of a trusted health professional, such as their local general practitioner; and v) be able to access the Internet in a private location (see also *Access considerations* below). Children will be eligible if they are aged 7 to 15 years and, in the opinion of the parent, are capable of reading at a Grade Two level. In this study, we are interested in parents of young cancer survivors aged less than 16 years, and so we matched siblings to this age range. Child participants will require parental consent.

